## Abstract

**Background:**

Over the past two or three decades, the prevalence of asthma has significantly increased worldwide; therefore, effective treatment without side effects is of utmost importance. Traditional Chinese medicine (TCM) plays a vital role in reducing symptoms and improving the quality of life in persistent-asthma patients. The aim of this study is to evaluate the efficacy of the *Jia Wei Yang He* (JWYH) formula in the treatment of asthma and to explore the relationship between the airway microbiome and TCM treatment in asthma patients.

**Methods/design:**

This multicenter, parallel-arm, randomized, double-blinded, placebo-controlled trial will assess the efficacy of JWYH in asthma patients with usual care. Persistent-asthma patients without life-threatening disease will be enrolled on a random basis and are equally assigned to a high- or a low-dose JWYH plus usual care group, or a placebo plus usual care group. Patients are followed up for 4 months. Accordingly, 240 patients will yield sufficient statistical power to determine a difference between groups. Based on modified intent-to-treat (mITT) analyses, the three groups will be compared at 4 weeks after the beginning of treatment. The primary efficacy measurement is the mean change in the Asthma Control Test (ACT) score from baseline to 4 weeks post treatment. Secondary outcomes include forced expiratory volume in 1 s (FEV_1_), forced vital capacity (FVC), peak expiratory flow (PEF), and asthma exacerbations.

This trial also includes analyses of the associations between airway microbiome and asthma treatment.

**Discussion:**

In this study, a randomized clinical trial design is described. The results are based on several outcomes that estimate the efficacy of the JWYH formula and prospective links between the airway microbiome and asthma treatment.

**Trial registration:**

ClinicalTrials.gov, ID: NCT03299322. Registered on 3 October 2017.

**Electronic supplementary material:**

The online version of this article (10.1186/s13063-018-2739-8) contains supplementary material, which is available to authorized users.

## Background

Asthma is a chronic airway inflammatory disease, symptoms of which include recurrent episodes of wheezing, breathlessness, chest tightness, and coughing [1]. In general, these symptoms are associated with airway hyperactivity and accompanied with variable and often reversible airflow obstruction [1]. In recent decades, the incidence of asthma has been significantly increased, and is estimated to affect 300 million individuals worldwide, including both adults and children [2]. According to the guidelines for managing asthma in China, the prevalence of asthma in the adult population is 1.24%, and during the past 30 years, the prevalence has increased [3]. The rising incidence of asthma in the developed world indicates that the control and treatment of asthma is still inadequate; therefore, the current treatment regimen needs to be further improved [4, 5].

As recommended by the Global Initiative on Asthma (GINA) guidelines, inhaled corticosteroids (ICS) and long-acting β_2_-adrenoceptor agonists are the treatment of choice for most patients with asthma [1]. Several patients may benefit from these treatments; however, the condition of many patients is not effectively controlled and their quality of life has not improved. In addition, several patients experience exacerbations because they do not tolerate treatment [6–8] or side effects, such as adrenal suppression, anaphylaxis, and osteoporosis that have been reported from long-term use of the above-mentioned medications [9–12].

Due to the chronic nature of asthma combined with the lack of satisfying and curative treatment, many asthma patients seek traditional Chinese medicine (TCM) as a complementary and alternative medicine (CAM) treatment [13, 14]. A previous study shows that the use of CAM in asthma patients ranged from 4 to 79% [15]. Since 2005, several double-blind, placebo-controlled clinical studies have demonstrated the efficacy and safety of herbal medicines for treating asthma [13, 14, 16, 17]. Data from these studies show that herbal medicine intervention is a safe and effective alternative medicine for the treatment of asthma.

In recent years, many studies that focus on TCM suggest that recurrent asthma has important links with wind (*Feng*), phlegm (*Tan*), blood stasis (*Yu*), and deficiency (*Xu*) [18]. In the Qing dynasty in China, a prescription of the *Yang He* (YH) formula was developed, and was commonly used for the treatment of the *Yin* and *Han* syndromes [19]. It functions in reinforcing deficiency (*Fu Zheng*), as well as dispelling wind (*Qu Feng*), removing blood stasis (*Hua Yu*), and eliminating phlegm (*Qu Tan*). Based on the empirical prescription, ingredients such as *Asari Radix Rhizoma* (*Xi Xin*) and *Codonopsis Radix* (*Dang Shen*) were added to improve the YH formula, thereby generating the *Jia Wei Yang He* (JWYH) formula [20, 21]. JWYH strengthens the function of reinforcing deficiency and resolving phlegm, and has been widely used for the treatment of chronic asthma. Our preliminary data show that the JWYH formula significantly improves cough and sputum symptoms, reduces the number of asthma episodes, and improves serum interferon (IFN)-γ levels (data not shown).

In several epidemiological studies, an association is reported between respiratory infections and the pathogenesis of bronchial asthma [22]. In addition, samples collected by bronchoscopy or induced sputum indicate a relation between asthma and microbial infection of the airway pathogens, including common bacteria such as *Proteobacteria*, *Bacteroidetes*, and *Firmicutes* [23]. Based on these previous observations, we hypothesize that TCM treatment modulates airway micro-organisms, and changes both airway microbiome composition and function, thereby impacting the symptoms of asthma. To the best of our knowledge, changes in microbiome composition in the airways of asthma patients with TCM treatment have not yet been fully characterized.

In previous studies, it is shown that JWYH therapy improves the symptoms of asthma and prevents the condition from worsening [18]. However, no data are available from large-scale randomized controlled trials (RCTs) on the efficacy of JWYH and its adverse effects. Therefore, we aim to perform the first double-blinded, randomized, placebo-controlled trial to determine the effectiveness and safety of JWYH treatment for persistent asthma.

## Methods/design

### Study design

This study is a multicenter, double-blinded, placebo-controlled, randomized, 4-week treatment clinical trial. The course of the study consists of three periods: a 1- to 3-day screening period, a 4-week primary treatment period, and a 3-month follow-up period. Follow-up assessments will be conducted at monthly clinic visits and will last for 3 months (Fig. 1). In this study, the clinical efficacy of JWYH is assessed in the treatment of asthma, identifying associations between the airway microbiome and asthma, and to examine if changes in the airway microbiome occur for asthma patients who receive daily TCM treatment.

**Fig. 1 Fig1:**
[figure not shown]
Illustration of study design for clinical studies

### Organization

The principal investigator (PI) is responsible for the overall project and for organizing Steering Committee meetings. PIs of sub-center departments are responsible for gathering experts to carry out the project. An independent Steering Committee will be responsible for the overall safety of participants, coordination of study meetings, feedback progress of recruitment or follow-up of participants, supervising the study, and overseeing quality control studies. The coordinating center is responsible for communicating protocol modifications and for providing materials.

### Setting

This clinical trial will be conducted in eight clinical centers in Shanghai: Longhua Hospital affiliated Shanghai University of TCM, Fengxian District TCM Hospital, Jing’an Centralized Hospital, Pudong Hospital, Eighth People’s Hospital of Shanghai, Shanghai TCM-Integrated Hospital, Xuhui Centeralized Hospital, and the Fudan University affiliated Zhongshan Hospital. Prior to the trial, all personnel are trained in the Longhua Hospital to ensure that the multicenter physicians and staff involved in the trial fully understand all aspects of the trial.

### Aims

#### Primary outcome

The primary outcome for the assessment of effectiveness includes mean differences in the Asthma Control Test (ACT) score between JWYH-treated and placebo-treated groups at week 4 from baseline. The ACT involves a five-question, patient-based tool for identifying patients with poorly controlled asthma. This score shows to be a reliable and valid measure that has been used to accurately evaluate changes in asthma control in different patient populations over time [24–27].

#### Secondary outcomes

Secondary outcomes included:ACT score at week 8Asthma exacerbation rate (AER) at week 8Percentage changes in FEV_1_ from baseline at week-4 and week-8 follow-up visitsPercentage changes in FVC from baseline at week-4 and week-8 follow-up visitsChanges of fractional exhaled nitric oxide (FeNO) at week-4 and week-8 follow-up visitsDaytime and nighttime peak expiratory flow (PEF) at week-4 and week-8 follow-up visits

### Exploratory outcome

ACT score at week 16

Microbial diversity: We hypothesize that airway microbiota is different among TCM treatment and control groups regarding changes in microbial diversity. The composition and structure of the microbiome in induced sputum will be tracked using high-throughput *16SrRNA*-based gene analysis. Diversity index of evenness, richness, and abundance will be calculated to summarize and compare microbiomes at the operational taxonomic unit (OTU) level.

### Participants

Patients who meet the inclusion criteria and are not excluded by the exclusion criteria (Table 1) will be invited to participate in this study. Every year, the collaborating centers have many asthmatic outpatients and inpatients, which significantly facilitates subject recruitment. Prior to the start of the study, patients are informed of all aspects of the study. The PIs and/or research nurse explain the study in detail, answer questions, ensure that informed consent will be given by each patient, and that appropriate signatures are obtained prior to the start of the study.

**Table 1 Tab1:** Inclusion and exclusion criteria

Inclusion criteria	
1. Patient diagnosed with chronic persistent asthma	
2. Annual uncontrollable time ≥ 3 months	
3. Patients who have given written informed consent	
Exclusion criteria	
1. History of upper upper/lower respiratory infection in the previous 1 month	
2. History of long-term controller medication use for asthma (orally or intravenously administered corticosteroid therapy) within the preceding 1 month	
3. History of antibiotic use in the previous 1 month	
4. History of life-threatening asthma	
5. History of chronic lung diseases	
6. History of serious disease of the heart and cerebrovascular disease	
7. History of severe liver or renal dysfunction or disease	
8. History of severe disease in the hematopoietic system	
9. History of immunodeficiency (including, but not limited to, HIV-positive detection)	
10. History of any other condition (such as known drug or alcohol abuse or psychiatric disorder)	
11. Are currently enrolled in, or discontinued within the last 30 days from, a clinical trial involving an investigational product or non-approved use of a drug or device	
12. History of allergies to the component of the investigational drugs	
13. Smoking within the past year	
14. Contraindication to induced sputum collection method on history or examination	
15. Any serious medical condition which, in the opinion of the investigator, would pose a significant risk to the patient or interfere with the interpretation of safety, efficacy, or pharmacodynamic data	

After the informed consent form (ICF) is signed and dated, a patient is considered “eligible” to enter the trial, is assigned a patient number, and is randomized to one of three treatment arms.

The two primary resources for identifying and recruiting potential subjects are as follows:Participants are recruited from the outpatient departments of the eight clinical centers in ShanghaiWe advertise in Longhua official accounts on WeChat and distribute printed posters in public clinics and nearby communities

We will continue to provide additional health care or compensation for participants’ health care needs that arise as a direct consequence of trial participation.

### Treatments administered

Patients are randomly assigned to groups to either receive a high-dose JWYH by oral administration, a low-dose JWYH by oral administration, or a placebo twice daily for 4 weeks (28 days). After baseline assessment, all participants will maintain or receive background therapy with ICS or a β_2_-adrenoceptor agonist as usual care.

Participants in the high-JWYH-formula group receive 18.5 g JWYH granules twice daily for 4 weeks, whereas participants in the low-JWYH-formula group receive 9.25 g of JWYH granules twice daily for 4 weeks. Patients in the placebo group are given placebo granules (9.25 g twice daily for 4 weeks). Drugs are identical in appearance, shape, size, and packaging.

Whole ingredients of the intervention formula include *Rehmanniae Radix Praeparata* (*Shu Di Huang*) 15 g, *Cinnamomi Cortex* (*Rou Gui*) 3 g, *Ephedrae Herba* (*Ma Huang*) 4.5 g, *Cervi Cornus Colla* (*Lu Jiao Jiao*) 3 g, *Sinapis Semen* (*Bai Jie Zi*) 6 g, *Zingiberis Rhizoma Preparatum* (*Pao Jiang*) 6 g, *Clycyrrhizae Radix Et Rhizoma* (*Gan Cao*) 6 g, *Asari Radix Rhizoma* (*Xi Xin*) 3 g, and *Codonopsis Radix* (*Dang Shen*) 9 g. All herbal granules are produced by the Sichuan Green Pharmaceutical Technology Development Limited by Share Ltd. in Sichuan, China. The dosage for all three groups includes one pack of granules that needs to be soaked in 100 mL of boiling water, taken orally twice daily, after breakfast and supper.

At each study visit, adherence to intervention is monitored and participants are asked to return all study containers with any unused packs of granules, including all empty containers. Once the patient is randomized, study sites will take every reasonable effort to follow the patient for the entire course of the study. All examination and transportation costs are covered and the results of symptoms and physical examinations will be explained at every visit. Prior to every visit, messages will be sent through WeChat or by phone to remind patients of the upcoming data collection.

Patients who discontinue the assigned treatment based on serious adverse events (SAEs), or poor compliance (more than 14 days without taking medicine), or in cases when the attending physician requests that the patient should undergo orally or intravenously administered corticosteroid therapy because symptoms worsen after screening.

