### Data collection and management

After screening and completing a set of questionnaires and evaluations, participants will attend two assessment visits and three follow-up visits (Fig. 2). Demographic information (date of birth, gender, etc.) and medical condition (medical history, concomitant medication, etc.) are recorded.

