### Sample size

Sample size calculations are based on the primary endpoint (ACT score at 4 weeks). At the 5% significance level, a total of 64 patients per group is required to achieve 80% power and to determine an increase of 2 points in the ACT score between the high-dose TCM plus usual care group and the placebo plus usual care group, assuming that the standard deviation of the groups is equal to 4 [30]. If the previous hypothesis is rejected, then the difference of 1.5 points in ACT score between the low-dose TCM plus usual care group and the placebo plus usual care group at the 5% significance level is tested. With an estimated dropout rate of 20%, a total of 240 patients is enrolled. If the initial hypothesis is not rejected, subsequent comparison is considered exploratory, and no conclusion is made [31, 32].

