### Statistical methods

The modified intent-to-treat (mITT) population is defined as randomized patients who receive at least one dose of randomized treatment with at least one post-randomization ACT value, classified according to their assigned treatment. The mITT analysis set is used for efficacy and exploratory analyses. Last observation carried forward (LOCF) imputation is used for missing data in the mITT population. A per-protocol (PP) population is defined as randomized patients without major protocol violations. The PP analysis set is used to repeat the efficacy analysis and to assess the robustness of the results. The safety population is defined as all patients who receive at least one dose of randomized treatment and for whom any post-dose data are available, classified according to the treatment received. The safety population will be used for the analyses of all safety measures.

For the primary outcome, changes in ACT scores from baseline to week 4 will be analyzed by means of analysis of covariance (ANCOVA). Treatment and center interactions will be examined, and, when an interaction does not exist, the ANCOVA model includes treatment and baseline ACT total score as explanatory variables. Otherwise, ANCOVA analysis will include the baseline ACT total score as covariate, treatment as a fixed effect, and the center as a random effect. Secondary outcomes (ACT at 8 weeks, FEV_1_, and FVC) are assessed in a similar fashion. AER will be analyzed using a *t* test or Wilcoxon rank-sum test as appropriate, and the Holm-Bonferroni method is used to control type I errors if necessary.

A mixed-model repeated measures (MMRM) analysis will be used to assess PEF changes. Comparisons will be based upon the contrast between treatments at week 4 (day 28) and week 8 (day 56). Model-based point estimates, 95% confidence intervals, and *p* values will be calculated. A *p* value < 0.05 is considered statistically significant.

For exploratory analysis, MMRM analysis uses all available ACT total score through the week 16 (day 112) visit, and comparisons will be based upon the contrast between treatments at week 16 (day 112). Model-based point estimates, 95% CIs, and *p* values are calculated.

Any adverse event will be recorded in the CRF regardless of relationship to the study intervention. Safety endpoints will be analyzed using summary statistics (frequency, count, percentage).

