Where appropriate, subgroup analyses, will be provided for effectiveness and safety endpoints, and will be based on baseline disease characteristics.

Data are analyzed using SAS 9.4 software (SAS Institute Inc., Cary, NC, USA). Unless otherwise noted, all treatment effects are employed at a two-sided α level of 0.05 and confidence intervals (CIs) will be calculated at 95%, two-sided.

For exploratory analysis of the airway microbiome, alpha diversity will be estimated as the number of observed OTUs and by the Chao1 Index, Simpson Index, Shannon Index, and phylogenetic alpha diversity (PD). UniFrac beta-diversity metrics will be compared between treatment groups using the PERMANOVA test from R’s vegan library [33]. In addition, UniFrac measures the phylogenetic distance between two samples as the fraction of the branch length of the phylogenetic tree, and are widely used to determine whether communities are significantly different [34]. Community dissimilarities will be estimated using principal coordinates analysis (PCoA). OTU abundance differences will be analyzed by assuming rarefied (Fisher’s exact test, respectively) and non-rarefied (metagenomeSeq zero-inflated Gaussian [35]) data. Statistical significance is determined by permutation tests using 10,000 permutations. In addition, core microbiome analyses will be performed to identify resident bacteria, after applying Benjamini-Hochberg FDR adjustments for multiple comparisons.

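### The primary ANCOVA omits background-therapy status at entry, forgoing some precision but introducing no bias

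*Protocol article*

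**What the plan says.** - **Background therapy.** Under Treatments administered, once baseline has been assessed, "all participants will maintain or receive background therapy" with ICS or a beta2-agonist. Some patients carry on with what they take and others begin.
- **Who can enter.** The controller-therapy exclusion in Table 1 names only oral or intravenous corticosteroids in the preceding month, so patients with and without prior inhaled therapy are eligible. Study design gives a screening period of 1 to 3 days, so there is no run-in on stable therapy.
- **What is recorded.** Data collection and management states that "medical condition (medical history, concomitant medication, etc.) are recorded".
- **Primary model.** Under Statistical methods, if treatment and center do not interact, "the ANCOVA model includes treatment and baseline ACT total score as explanatory variables". If they do, center is added as a random effect. Background therapy appears in neither version. Week-8 ACT, FEV1 and FVC are handled similarly.
- **Randomization.** It follows screening and baseline assessment. No stratification by background therapy is stated.
- **Planning figures.** Sample size states: "At the 5% significance level, a total of 64 patients per group is required to achieve 80% power", for "an increase of 2 points in the ACT score" (high dose against placebo), "assuming that the standard deviation of the groups is equal to 4". The second step tests "the difference of 1.5 points in ACT score between the low-dose TCM plus usual care group" and placebo.

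**The concern.** The Background section calls ICS and long-acting beta2-agonists the treatment of choice for most patients. On the protocol's own view, then, starting background therapy may itself move the ACT within the 4-week primary window. Two patients with the same baseline score, one already treated and one about to start, can have different expected changes, and baseline ACT alone does not separate them. Any such difference that the model does not explain stays in the residual variance.

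What is at stake is precision, above all for the low-dose comparison, where power is already low. The point concerns stated text and not a detail left to an unseen analysis plan, because the protocol itself names the covariates of the primary model.

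**Working it through.** **Inputs from the protocol.** Two-sided alpha 0.05 ("all treatment effects are employed at a two-sided α level of 0.05"); 64 analyzed per arm; SD 4; differences of 2 points (high dose) and 1.5 points (low dose); 20% dropout; 240 in total.

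**Assumed inputs, not in the documents.** Share of patients starting background therapy, p = 0.2 to 0.5. Extra 4-week ACT gain of starters over continuers, d = 1, 2 or 3 points.

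**1. The plan's own figure.** By the normal approximation, n = 2 × (1.960 + 0.842)² × 4² / 2² ≈ 62.8, so 63 per arm. The t-test gives 63.8, so 64. Power at 64 per arm is 80.1%. With dropout, 64 / 0.8 = 80 per arm, and 3 × 80 = 240. The stated figures reproduce. For 1.5 points at the same n and SD, power is 55.8%.

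**2. Variance due to starting or continuing.** A two-group mixture with share p and mean difference d adds p(1 − p)d² to the variance of the change within an arm.

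**3. Reading A: SD 4 is the total SD within an arm.** Planned power stays at 80.1%. Adjustment leaves a residual SD of √(16 − p(1 − p)d²). For example, p = 0.5 and d = 3 give √(16 − 2.25) = 3.708.

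| d | p | Adjusted SD | Power, 2 points | Power, 1.5 points |
|---|---|---|---|---|
| 1 | 0.2 | 3.980 | 80.5% | 56.2% |
| 1 | 0.5 | 3.969 | 80.8% | 56.4% |
| 2 | 0.2 | 3.919 | 81.7% | 57.5% |
| 2 | 0.5 | 3.873 | 82.6% | 58.5% |
| 3 | 0.2 | 3.816 | 83.7% | 59.7% |
| 3 | 0.5 | 3.708 | 85.7% | 62.2% |

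**4. Reading B: SD 4 applies within each background-therapy stratum.** The unadjusted SD is then √(16 + p(1 − p)d²), and power for 2 points without the factor is:

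| d | p = 0.2 | p = 0.5 |
|---|---|---|
| 1 | 79.8% | 79.5% |
| 2 | 78.6% | 77.7% |
| 3 | 76.7% | 74.8% |

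**5. Check by simulation (reading A, p = 0.5).** ANCOVA on treatment and baseline, without and with the factor, gave 79% and 82% power at d = 2, and 80% and 85% at d = 3. Under no treatment effect with d = 3, type I error was 5.0% and 5.1%. So the omission costs precision, not validity.

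**6. What is left out.** Steps 3 and 4 use a two-sample comparison and give baseline ACT no credit. If SD 4 is unadjusted and baseline ACT correlates 0.3 or 0.5 with the change (an assumption), the planned ANCOVA already reaches 83.7% (SD 4 × √(1 − 0.09) = 3.816) or 90.0% (SD 4 × √(1 − 0.25) = 3.464).

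**The case against.** The planned ANCOVA is a valid analysis, and most trials record further baseline variables that might add precision. Several specific objections carry weight.

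- **Power below 80%.** A reader might infer that the omission takes the trial below its planned power. The protocol does not support that. It gives 4 as the SD of the groups, and in that sentence the groups are the treatment arms, so any mix of starters and continuers is already inside it. The shortfall in step 4 needs the less natural reading.
- **Bias.** A reader might also infer a biased treatment effect. Randomization follows the baseline assessment, so status at entry is balanced in expectation.
- **Two losses.** Residual spread and chance imbalance between arms can look like separate costs. They are the same variance: the unadjusted standard error already allows for chance imbalance.
- **Unknown inputs.** Neither p nor d is in the documents. At d = 1 the gain is under one percentage point of power. If untreated patients enter with lower scores, baseline ACT absorbs part of the difference.
- **Imperfect factor.** Status at screening only approximates who starts. A patient on a beta-agonist alone may simply continue it or may newly receive ICS, so adjustment need not capture the whole difference.
- **Timing of the record.** The text does not say that concomitant medication is recorded before randomization or by drug class, and the schedule figure is not shown. This is an inference.

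All of these limit the size of the point. None makes the covariate harmful. The subgroup analyses by baseline characteristics that the protocol mentions do not alter the primary model.

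**Conclusion.** The point holds as an inexpensive improvement, not as an error that invalidates the plan. The protocol allows background therapy to be started or continued after baseline and then fixes a primary model that does not distinguish the two.

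On the natural reading of SD 4, the stated power stands. What is forgone is less than 1 percentage point of power at d = 1, about 1.6 to 2.5 points at d = 2, and about 3.6 to 5.6 points at d = 3, for 20–50% starters. At 1.5 points the gain is at most about 6 percentage points (55.8% to 62.2%), so adjustment helps the low-dose step but does not make it well powered. Only if SD 4 describes patients within a background-therapy stratum would unadjusted power fall below 80%, to about 75–79% at d = 2 to 3.

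These sizes rest on assumed p and d, on a factor that fully separates starters from continuers, and on no contribution from baseline ACT. The real gain may be smaller.

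**What to change.** In Statistical methods, add background therapy at screening, before randomization (on ICS; on beta-agonist only; on neither), as a pre-specified fixed factor. Include it in both versions of the primary ANCOVA and in the corresponding models for week-8 ACT, FEV1 and FVC.

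Use pre-randomization status only. Changes in therapy after randomization may be affected by the assigned treatment and should not be covariates. Confirm that the concomitant-medication record captures drug class before randomization.

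A three-level factor costs two degrees of freedom (one if reduced to two levels). It needs no extra patients or visits. The article describes recruitment as ongoing with no interim analysis planned, so the factor can be fixed before unblinding; introduced afterwards, it would be a post hoc adjustment.

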### Randomization and blinding

For each group, a block randomization list is provided, which is generated prior to initiation of the study using a random seed number via SAS PROC PLAN software (SAS Inc., Cary, NC, USA). Randomization occurs after screening and baseline assessments, and patients will be randomized in a 1:1:1 fashion to receive one of three treatments. Participants will be randomized using web-based randomization service, which is an online, central randomization service provided by Longhua Clinical Trials Support Unit in Shanghai, China. This service will not release the randomization sequence until the interventions are assigned.

All investigators involved will be blinded to group assignment. An independent data analyst and the research nurse who assigns subjects will not be blinded to treatment status and will not take part in any other part of this trial.

If, after the first administration, any clinically significant adverse event is potentially related to JWYH treatment, the study physician will re-evaluate the participant and local PI or delegate will decide whether a non-blinded procedure is necessary. If non-blinding is considered required, the actual allocation information will be provided to the physician.

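### Stated granule masses contradict the claim of identical products: placebo is matched in mass to the low dose only, which puts blinding of the powered high-dose versus placebo comparison at risk

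*Protocol article*

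**What the plan says.** The product description is in one section of the protocol article, Treatments administered:

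- High dose: "Participants in the high-JWYH-formula group receive 18.5 g JWYH granules twice daily for 4 weeks".
- Low dose: "participants in the low-JWYH-formula group receive 9.25 g of JWYH granules twice daily for 4 weeks".
- Placebo: "Patients in the placebo group are given placebo granules (9.25 g twice daily for 4 weeks".
- Preparation: "The dosage for all three groups includes one pack of granules that needs to be soaked in 100 mL of boiling water".
- Matching: "Drugs are identical in appearance, shape, size, and packaging".

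Study design calls the trial double-blinded ("This study is a multicenter, double-blinded, placebo-controlled, randomized, 4-week treatment clinical trial"), and Randomization and blinding adds "All investigators involved will be blinded to group assignment". No second placebo matched to 18.5 g, no double-dummy scheme and no filler is described.

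The primary outcome is the change in ACT score at week 4. Primary outcome describes the instrument thus: "The ACT involves a five-question, patient-based tool for identifying patients with poorly controlled asthma". Sample size makes high dose versus placebo the first test and the one that sets the trial's size. Low dose versus placebo is tested formally only if the first null hypothesis is rejected; otherwise it is exploratory.

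**The concern.** The statements on mass, on one pack per intake and on identical products cannot all be taken at face value. If each intake is one pack, the high-dose pack carries double the granules of the placebo pack, and double the solids go into the same 100 mL. Identical outer sachets would not equalise weight, fill or the contents of the cup.

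The mismatch falls on the comparison that matters most. The ACT is answered by the patient, so a patient's belief about treatment can move the score directly. High dose versus placebo carries the power calculation and opens the test sequence. If allocation could be suspected in that pair, part of an observed difference might be expectation rather than drug effect, and the planned analysis could not separate the two.

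The Discussion faults earlier trials of the parent formula for not being double blinded and presents this trial as high-quality evidence for that reason. The matching claim therefore supports the trial's main conclusion.

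**Working it through.** **Inputs (protocol article)**

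- Mass per intake: 18.5 g high dose, 9.25 g low dose, 9.25 g placebo; twice daily for 28 days; one pack per intake (Treatments administered).
- Difference 2 ACT points, SD 4, 5% level, 80% power, 64 per group, 20% dropout, 240 in total (Sample size).
- Two-sided testing (Statistical methods).

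**Step 1: the plan's own figure.** The standardised difference is 2/4 = 0.5. The normal approximation gives 63 per group. The exact t-test calculation gives 63.77, so 64, with power 80.1%. Allowing for dropout, 64/0.80 = 80 per arm, and 3 × 80 = 240. The sample size reproduces and is not affected by this point.

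**Step 2: mass matching.**

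| Contrast | Per intake | Ratio | Per day | Over 28 days |
|---|---|---|---|---|
| High dose vs placebo | 18.5 g vs 9.25 g | 2.0 | 37 g vs 18.5 g | 1036 g vs 518 g |
| Low dose vs placebo | 9.25 g vs 9.25 g | 1.0 | 18.5 g vs 18.5 g | 518 g vs 518 g |

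**Step 3: can the statements be read so that they agree?**

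- *The gram figures are active content, and filler equalises the packs.* Placebo has no active content, so 9.25 g of placebo granules reads naturally only as fill weight. A high-dose pack must hold at least its 18.5 g.
- *The high dose is two packs of 9.25 g.* The arithmetic fits, but the text says one pack for all three groups, and a difference in pack count would itself be visible.

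Neither reading removes the conflict without changing a sentence.

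**Step 4: what a bias would do (assumption only).** The documents give no figure for expectation bias. Suppose there is no true effect and a bias of b points favours high dose.

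SE = 4 × √(2/64) = 0.707

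Rejection rate = P(Z > 1.96 − b/SE) + P(Z < −1.96 − b/SE)

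| Assumed b (ACT points) | b/SE | Two-sided false-positive rate |
|---|---|---|
| 0 | 0 | 5% |
| 0.25 | 0.354 | 6.4% |
| 0.5 | 0.707 | 10.9% |
| 1.0 | 1.414 | 29.3% |

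**Step 5: does it reach the low-dose claim?** In the fixed sequence, low dose is claimed only if both tests reject. Under the low-dose null, P(both reject) ≤ P(low-dose test rejects) ≤ 5%, however often the first test rejects wrongly. The low-dose and placebo packs are equal in mass, so the mass difference does not bias that test. Any inflation stays in the first comparison.

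**The case against.** The strongest reply is that the documents do not show anyone being unblinded. The design is parallel, so each patient sees one kind of pack and has nothing to compare it with. No section says that patients are told the pack mass of each arm. The matching sentence does not mention weight, and one sachet size can be filled to different levels. A journal article also commonly leaves packaging and pack handling to the full protocol.

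Much of this stands, and it limits the point. A reader might make four stronger inferences that the text does not support:

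- *The primary comparison is in fact unblinded.* The masses show a risk, not that patients or assessors identify their arm.
- *Packs of different weight cannot be the same size.* The outer sachets could be the same size; the conflict concerns their contents.
- *Site staff will recognise the high-dose arm from returned packs.* Unused packs are returned at visits, but the article does not say who receives them or whether that person assesses outcomes. Randomization and blinding makes the assigning nurse unblinded by design, with no other part in the trial.
- *The bias carries over into the low-dose claim.* It does not, by Step 5 of the working.

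The reply does not remove the contradiction. This is not a detail left out: the article itself states the masses, the single pack and the identity of the products, and they do not agree.

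**Conclusion.** The point holds as a contradiction within Treatments administered and a resulting risk to blinding. As written, placebo matches the low dose in mass (ratio 1.0) but not the high dose (ratio 2.0), and the unmatched pair is the powered, first-tested comparison on a patient-reported score. The sample size and the error rate of the low-dose claim are unaffected.

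The size of any bias is unknown. The range from 5% (no bias) to 29.3% (1.0 point) rests wholly on assumed biases, with 64 per arm, SD 4 and a normal approximation. It shows how sensitive the primary test would be and does not estimate what will happen. The documents also do not settle whether the masses, the one-pack statement or the matching statement is misreported, and this review takes no position on which is right.

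**What to change.** Reconcile three statements in Treatments administered: the granule mass per intake in each arm, the single pack for all groups, and the identity of the products. This is a clarification of the text and leaves each arm's active content as the sponsor has specified it.

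If the clarification shows that the packs are matched in mass, the corrected text settles the matter.

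If the packs do differ in mass:

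- do not describe high dose versus placebo as fully double-blind, and state the mass difference as a limitation;
- report the mass-matched low-dose versus placebo contrast beside the primary result, labelled exploratory if the first test fails, as the plan already requires.

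That contrast supports interpretation but does not replace the primary one. It concerns a different dose, and at 64 per arm its power for the planned 1.5 points is about 56% (1.5/0.707 = 2.12; P(Z > 1.96 − 2.12) ≈ 0.56). A non-significant low-dose result would therefore not show that a high-dose effect was due to bias.

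The cost is a short protocol clarification and a few sentences in the report, with no extra patients, visits or analyses. Trial status says recruitment is under way, so repacking would put two presentations into one trial; that is a larger decision and is not asked for here.
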